### Study visits

Physicians blinded to the intervention will perform study documentation and patient assessment. Since the trial is designed as an observer and patient blinded RCT, information about the surgical procedure will not be disclosed during the follow-up examinations to any assessors. There will be 11 study visits in total. The study design flow diagram is presented in Table 1. Potential study participants will be identified by the preoperative outpatient clinic consultations. The first visit will be preoperative after informed consent is obtained. Then patients will receive their study intervention according to the preoperative randomization. Postoperatively, study visits will be performed at discharge, 3, 6, 9, 12, and 18 months and 2, 3, 4, and 5 years. Each study visit includes data collection of weight, blood tests (e.g., hemoglobin, creatinine, urea, uric acid, calcium, C-reactive protein, albumin, liver function tests, fasting glucose, HbA1c, vitamins A, B1, B6, B12, and D, parathormone, ferritin, folate, zinc, cholesterol, lipoproteins, and triglycerides), and complications. In addition, questionnaires will be also assessed to study the quality of life (Bariatric Analysis and Reporting Outcome System [BAROS] [18] and the Gastrointestinal Quality of Life Index [GIQLI] [19]), the Arts questionnaire [20] to determine postoperative determine dumping syndrome and questionnaire for quantification of frequency and severity of potential diarrhea.

**Table 1 Tab1:** Schedule of study assessments

Study periods	Screening	Intervention	Follow-up								
Visit	1	2	3	4	5	6	7	8	9	10	11
Time (day, month, year)	− 3 months	0–5 days	3 months	6 months	9 months	1 year	1.5 years	2 years	3 years	4 years	5 years
Patient information and informed consent	x										
Demographics	x										
Medical history	x										
Inclusion/exclusion criteria	x	x									
Physical examination	x	x	x	x	x	x	x	x	x	x	x
Vital signs	x	x	x	x	x	x	x	x	x	x	x
Laboratory tests	x	x	x	x	x	x	x	x	x	x	x
Randomization		x									
Operation		x									
Complications		x	x	x	x	x	x	x	x	x	x
Primary variables	x	x	x	x	x	x	x	x	x	x	x
Secondary variables	x	x	x	x	x	x	x	x	x	x	x
Questionnaires	x			x		x		x	x	x	x
Adverse events		x	x	x	x	x	x	x	x	x	x

### Study endpoints

#### Primary endpoint

The primary endpoints are %TWL and the number of nutritional deficiencies 1, 3, and 5 years postoperatively. For the %TWL the presurgical weight (at hospital entry time of the patient) and postsurgical weight at the corresponding visit will be measured.

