**Methods/design:**

The trial is designed as a multicenter, randomized, patient- and observer-blinded trial. The relevant ethics committee has approved the trial protocol. To demonstrate that long BPL RYGB is superior compared to short BPL RYGB in terms of weight loss and resolution of T2DM, the study is conducted as a superiority trial. Postoperative percent total weight loss and nutritional deficiency rate are the primary endpoints, whereas morbidity, mortality, remission of obesity-related comorbidities and quality of life are secondary endpoints. Eight hundred patients, between 18 and 65 years and with a body mass index (BMI) from 35 to 60 kg/m^2^ who meet the regulatory rules for bariatric surgery in Switzerland, will be randomized. The endpoints and baseline measurements will be assessed pre-, intra-, and postoperatively.

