### Primary objective

The primary objective of this study is to show that long BPL leads to a greater percent total weight loss (%TWL, superiority), while not leading to a larger nutritional deficiency rate (non-inferiority) at 1-, 3-, and 5-year follow-up.

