### Statistical analyses

#### Sample size

Our study was designed to evaluate whether long BPL in RYGB has advantages compared to short BPL in terms of % weight loss (superiority) without compromising the safety in terms of nutritional deficiency rate (non-inferiority) at 5 years follow-up. For our primary outcome efficacy and safety, assuming a %TWL of 27 ± 10% at 5 years follow-up for short BPL with a minimal improvement of 5% TWL for long BPL to be relevant and an expected cumulative nutritional deficiency rate of 50% at 5 years follow-up with a non-inferiority margin defined at 10%, 400 patients per group will be needed to reach a power of 80% with an alpha level at 5%. For further details on calculations, see the “Analysis of endpoints” section below.

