#### Analysis of primary endpoint

The primary objective consists of two separate analyses, one for safety and one for efficacy. The difference in efficacy is tested by performing a Mann-Whitney *U* test, thereby releasing the assumption of normality for the proportion of weight loss. The proportion of safety events during the first 5 years in each study arm is reported, including the two-sided 95% confidence interval.

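### The primary endpoints are set at 1, 3 and 5 years, with deficiency worded as a number, but 400 per group is sized for one 5-year cumulative deficiency proportion

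*Protocol article*

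**What the plan says.** Four sections of the protocol article describe the primary comparison.

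- **Primary objective.** Superiority on %TWL is to be shown "while not leading to a larger nutritional deficiency rate (non-inferiority) at 1-, 3-, and 5-year follow-up". Deficiency is a rate, and three times are named.
- **Primary endpoint.** "The primary endpoints are %TWL and the number of nutritional deficiencies 1, 3, and 5 years postoperatively". The same three times are named, but deficiency is now a number.
- **Sample size.** The weight-loss advantage is to be shown "without compromising the safety in terms of nutritional deficiency rate (non-inferiority) at 5 years follow-up". The planning values are also for 5 years: "assuming a %TWL of 27 ± 10% at 5 years follow-up for short BPL" and "an expected cumulative nutritional deficiency rate of 50% at 5 years follow-up", with a margin of 10%. A relevant %TWL gain of 5, 80% power and a 5% alpha lead to 400 per group.
- **Analysis of primary endpoint.** %TWL is compared by one Mann-Whitney test with no time attached. For safety, "The proportion of safety events during the first 5 years in each study arm is reported", with a two-sided 95% confidence interval.

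**The concern.** Two features of the primary comparison differ between sections.

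**Time.** The objective and the endpoint definition put 1, 3 and 5 years on an equal footing. The sizing uses 5 years alone. Nothing in the article ranks the three times or says that 5 years decides.

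**Measure.** A 50% rate with a 10% margin has meaning for a proportion of patients. It has none for a count of deficiencies, which is what the endpoint definition literally says. A cumulative proportion to 5 years also differs from status at the 1-, 3- or 5-year visit: a deficiency present at year 1 and later resolved counts in the first but not in the 5-year status.

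What the trial may conclude therefore depends on which section is followed. Requiring success at all three times means the stated power is not delivered. Accepting success at any one time raises the false-positive rate. If the point stays open until data are seen, the time and the measure could be chosen after the fact.

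**Working it through.** **Inputs from the Sample size section:** deficiency rate 50% in both arms, margin 10% (read as 10 percentage points), %TWL SD 10, %TWL difference 5 (read as percentage points), 400 per group, 80% power, alpha 5%. The two-sided 95% interval in the Analysis of primary endpoint section corresponds to one-sided 2.5% for non-inferiority.

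**Step 1: reproduce the 400.**

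n per arm = (1.960 + 0.842)² × [0.5×0.5 + 0.5×0.5] / 0.10² = 7.849 × 0.5 / 0.01 = 392.4, so 393.

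At 400 per arm the standard error is √(0.5/400) = 0.03536 and the standardised margin is 0.10/0.03536 = 2.828. Power = Φ(2.828 − 1.960) = 80.7%. The plan's figure is reproduced. One-sided 5% would need only 310.

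**Step 2: what %TWL needs.**

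n per arm = 2 × 10² × 7.849 / 5² = 62.8, so 63 (about 66 to 73 with an efficiency allowance for the Mann-Whitney test). At 400 per arm, power exceeds 99.9%. The deficiency proportion at 5 years therefore sets the sample size, and power for both co-primaries together stays at about 80.7%.

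**Step 3: non-inferiority required at 1, 3 and 5 years.** The article gives no rates at 1 and 3 years and no correlations between times, so these are assumptions. Power is the probability that three equally correlated normal statistics all exceed 1.960, with the 10-point margin at each time and 400 per arm. The standardised margin is 2.828 at a rate of 50%, 2.887 at 40% and 3.086 at 30%.

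| Assumed rates at 1/3/5 years | Correlation 0.7 | Correlation 0.9 |
|---|---|---|
| 50/50/50% | 67% | 73% |
| 30/40/50% | 70% | 76% |

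For a cumulative measure, the first row means that no further patient has a first deficiency after year 1, so the second row is the more natural one. Both fall short of 80%.

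**Step 4: success at any one time, unadjusted.** The claim of interest is long limb better, so the relevant error is one-sided at 2.5% per test. The probability that at least one of three null statistics exceeds 1.960 is 5.5% at correlation 0.7 and 4.2% at 0.9. This is for %TWL alone, before the non-inferiority condition is applied.

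**The case against.** The strongest reply is that the Sample size section makes the intention plain: 5 years is the design point and the rest is loose drafting. The article is condensed, and a rule for several time points may properly sit in a statistical analysis plan that is not shown. Deficiency is called a rate in the Abstract, the Primary objective and the Sample size section, and a proportion in the analysis section. Only the endpoint definition says number, and the article uses that word loosely elsewhere: the number of complications is to be tested by chi-squared or Fisher's exact test.

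Much of this stands. The missing multiplicity rule is not itself a fault here, and the wording on the measure is one departure rather than four rival endpoints. But an analysis plan cannot remove a conflict between the protocol's own objective and endpoint on one side and its sizing on the other. If 5 years was meant, the Primary objective and Primary endpoint sections are wrong as written.

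Stronger readings that a reader might infer, and that the documents do not support:

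- *Diabetes resolution is a further primary target.* The Abstract does describe the trial as testing whether the long limb is "superior compared to short BPL RYGB in terms of weight loss and resolution of T2DM, the study is conducted as a superiority trial". Its next sentence makes remission of comorbidities secondary, as do the Secondary objective and Secondary endpoints sections.
- *The analysis section contradicts three time points for %TWL.* It names no time for that test, so it leaves the question open.
- *The false-positive rate doubles from 5% to about 8.4–10.9%.* Those figures are for three two-sided tests at the same correlations and include results favouring the short limb. They also ignore that the objective joins superiority with non-inferiority, so they are not the trial's error rate.
- *The sample size is wrong.* It is correct for the single comparison that it describes.

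**Conclusion.** The contradiction is real and concerns the trial's primary decision. The stated 80% power belongs to a single 5-year cumulative proportion, not to the three-time endpoint set. Requiring non-inferiority at all three times would lower power from 80.7% to about 67–76% across the scenarios above. Accepting any one time would put false claims of %TWL superiority at about 4.2–5.5% against 2.5%. The sizes rest on assumed rates at 1 and 3 years, assumed equal correlations of 0.7–0.9, a 10-point margin at every time and no loss to follow-up. The conflict between sections rests on none of these. Power for %TWL is not in question at the planning effect.

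**What to change.** Align the text with the quantity already sized.

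- **Primary objective and Primary endpoint:** *The two co-primary endpoints are %TWL at 5 years and the cumulative proportion of patients with at least one nutritional deficiency by 5 years. Superiority on the first and non-inferiority on the second are both required.* Make the 1- and 3-year results and the count of deficiencies secondary.
- **Analysis of primary endpoint:** state 5 years for the Mann-Whitney test, and use the same name for the deficiency proportion as in the endpoint definition.

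The deficiency measure should not be narrowed further, for example to deficiencies that are new since surgery. The document has no such restriction, and the 50% rate behind the sample size might then no longer apply.

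**Cost.** Wording only; 400 per group stands (393 needed), and requiring both co-primaries needs no split of alpha between them. The price is that no confirmatory claim can be made at 1 or 3 years. Keeping all three times confirmatory would cost more. A Bonferroni split for non-inferiority, with 50% assumed at each time, leaves 66.8% power per comparison at 400 per arm, or needs 524 per arm.

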#### Secondary endpoints

%EBMILRemission of comorbiditiesComplication rateQuality of life

All comorbidities will be assessed at 3, 6, 9, 12, and 18 months and 2, 3, 4, and 5 years by a physician based on symptoms, laboratory findings, and use of medication. The postoperative course of comorbidities will be defined as follows: remission: no symptoms/without any medication (dyslipidemia true remission = no medication and normal lipid values); remission of T2DM will be defined according to the ADA criteria: complete remission: HbA1c < 6.0%, fasting glucose < 100 mg/dl and at least one year no active pharmacologic therapy; partial remission HbA1c < 6.5% [21]; improvement: less symptoms and/or less medical treatment/medication; unchanged: same symptoms and equivalent therapy; worsened: more symptoms or increase of therapy; de novo comorbidity: comorbidity not present at baseline, but newly developed within 5 years postoperatively. All surgical and non-surgical complications will be assessed according to the Clavien-Dindo classification (CDC) [22] and the Comprehensive Complication Index (CCI) [23]. The Arts score will help to identify potential dumping syndrome. BAROS and GIQLI scores will be used to measure postoperative quality of life.

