To this day, only one randomized controlled trial (RCT) [16] compared long BPL RYGB (150 cm BPL, AL 75 cm) with a short BPL RYGB (BPL 75 cm, AL 150 cm) in 128 patients and found a significant increase in percent excess weight loss (%EWL) for patients with long BPL RYGB in the first 4 years after surgery. However, the underlying mechanism of a greater weight loss after long BPL RYGB remains unclear. Furthermore, lengthening of the BPL cannot be done limitless as it carries an increasing risk of severe malnutrition. Neither of the two procedures seems to be technically more challenging, since the complication rates did not show any significant difference [16]. However, a limitation of this study was the cohort of 146, which was too small to show any advantage in terms of comorbidities resolution or quality of life changes.

Therefore, our aim is to investigate if a longer BPL in RYGB leads to greater weight loss and superior remission of comorbidities in morbidly obese patients without reducing its safety. No matter which outcome will be obtained, our results will provide level I evidence for an improvement of the standard laparoscopic RYGB and thus may potentially influence global bariatric surgery guidelines.

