### Secondary objective

The secondary objectives are to assess the percent excess body mass index loss (%EBMIL), remission of comorbidities, complication rate/safety, and quality of life 1, 3, and 5 years after long and short BPL RYGB.

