As total bowel length varies by many meters between individuals, measuring the total length and therefore knowing the dimensions of all segments involved in RYGB will lead to a better understanding of the role of each segment in the beneficial effects after RYGB. This study investigates the effectiveness of long BPL RYGB compared to short BPL RYGB, analyzing defined clinical endpoints such as weight loss, morbidity and mortality, improvement in obesity-related comorbidities, and quality of life. Furthermore, the RCT by Homan et al. [16] failed to show any significant differences in T2DM remissions as it was only powered for weight loss. Our study has enough power to address the postoperative course in terms of resolution of comorbidities.

In conclusion, the “perfect” RYGB leads to adequate %TWL and improvement in obesity-related comorbidities without increasing the complication rate. The SLIM trial will answer questions about effectiveness and safety after long BPL RYGB and provide level I evidence for improvement of the standard RYGB. These findings might therefore potentially influence bariatric surgery guidelines on a global level.

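### Outside dyslipidemia and T2DM, comorbidity remission needs no measured value, so usually silent disease that is left untreated counts as remitted

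*Protocol article*

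**What the plan says.** Under Secondary endpoints, the article has each comorbidity assessed at nine postoperative time points "by a physician based on symptoms, laboratory findings, and use of medication". It then defines the possible courses. The general rule is "remission: no symptoms/without any medication (dyslipidemia true remission = no medication and normal lipid values". T2DM has its own rule with laboratory thresholds: "complete remission: HbA1c < 6.0%, fasting glucose < 100 mg/dl and at least one year no active pharmacologic therapy". The remaining categories rest on symptoms and therapy alone: "improvement: less symptoms and/or less medical treatment/medication; unchanged: same symptoms and equivalent therapy; worsened: more symptoms or increase of therapy".

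Table 1 (Study visits) marks vital signs at every one of the 11 visits. No endpoint definition refers to them.

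The Background gives as the trial's aim to learn whether a longer biliopancreatic limb "leads to greater weight loss and superior remission of comorbidities in morbidly obese patients". The Secondary objective section lists "remission of comorbidities, complication rate/safety, and quality of life 1, 3, and 5 years after long and short BPL RYGB". The Analysis of secondary endpoints section names tests for %EBMIL and for complications, and leaves the other secondary endpoints to exploratory methods and graphs.

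**The concern.** For a condition that patients feel, absence of symptoms and of drugs is a fair proxy for remission. For a condition that is usually silent, the symptom criterion is met almost automatically, and the rule reduces to whether a drug is being taken. The endpoint then records prescribing rather than disease.

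The authors evidently saw this for lipids: they speak of true remission there and add normal values to the absence of medication. The same reasoning was not carried to other silent conditions, although the visit schedule would supply at least some of the measurements.

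At stake are the absolute remission percentages, which can be too high in both arms, and the comparison between arms, which can be distorted. The Discussion relies on this outcome when it states: "Our study has enough power to address the postoperative course in terms of resolution of comorbidities".

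**Working it through.** **1. What the rule demands of each condition (Secondary endpoints)**

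| Condition | Off medication | Measured value required |
|---|---|---|
| Dyslipidemia | yes | yes, normal lipids |
| T2DM, complete remission | yes, at least one year | yes, HbA1c and fasting glucose |
| Any other comorbidity | yes, if the slash means and | none |

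The slash in the general rule can be read as and or as or. The stricter reading (and) is used here. Under or, a symptom-free patient on full treatment would also be remitted, so the rule would be looser still.

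**2. Does the opening sentence close the gap?** It names symptoms, laboratory results and drugs as the basis of assessment. Vital signs are not laboratory results, and no laboratory value enters the general rule. Followed as written, a symptom-free, drug-free patient with a persistently abnormal reading is remitted.

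**3. Is the sample size involved?** The plan's figure is 400 per group. From Sample size: deficiency rate 50% in each arm, margin 10 points, power 80%, alpha 5%, taken here as one-sided 2.5%.

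n = (1.960 + 0.842)² × (0.5×0.5 + 0.5×0.5) / 0.10² = 7.85 × 0.5 / 0.01 ≈ 393 per group, close to 400.

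For %TWL (difference 5, SD 10): n = 2 × 7.85 × 10² / 5² ≈ 63 per group.

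Non-inferiority on deficiencies drives the number. Comorbidity remission plays no part in it.

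**4. Effect on the endpoint (illustration)**

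Let R be the true remission rate and f the share of truly non-remitted patients who are symptom-free and off drugs, equal in both arms.

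- Counted rate = R + (1 − R) f, so each arm is overstated by (1 − R) f.
- Counted difference = (R_A − R_B)(1 − f).

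Assumed, not in the document: R_A = 60%, R_B = 50%, and f from 0 to 0.4. Power is for a two-sided 5% comparison of two proportions, with an assumed 400 or 200 affected patients per arm.

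| f | Counted A | Counted B | Difference (points) | Power, 400 per arm | Power, 200 per arm |
|---|---|---|---|---|---|
| 0 | 60% | 50% | 10 | 81% | 52% |
| 0.1 | 64% | 55% | 9 | 74% | 45% |
| 0.2 | 68% | 60% | 8 | 66% | 38% |
| 0.3 | 72% | 65% | 7 | 57% | 33% |
| 0.4 | 76% | 70% | 6 | 48% | 27% |

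At f = 0.2 the overstatement is 0.40 × 0.2 = 8 points in arm A and 0.50 × 0.2 = 10 points in arm B. At f = 0.4 it is 16 and 20 points. Since 400 is the whole arm, the 400 column supposes that every patient has the comorbidity.

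**The case against.** **The article is condensed and names neither hypertension nor blood pressure.** The two conditions with specific rules both require measured values, and the full protocol may list further comorbidities with their own criteria. This stands as far as the example goes: hypertension is illustrative, and that vital signs include blood pressure is a natural but unstated reading. It does not remove the point, because the article states a general rule and presents it as the definition. The objection is to that rule, not to missing detail.

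**A physician makes the assessment, with examination and vital signs at the same visits.** Nothing tells the physician to ignore an abnormal reading, so some such patients may in practice not be called remitted. But nothing tells the physician to use the reading either, and no limit is given. Two centers could classify the same patient differently.

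**The consequence is limited.** This stands. The endpoint is secondary and exploratory. Patients and assessors are blinded, which makes misclassification favouring one arm less likely.

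Three stronger readings are tempting and are not supported:

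- A reader might infer that the arm difference must shrink. That follows only if f is an equal share of the non-remitted patients in both arms. If instead an equal share of those counted as remitted were false, the counted rate would be R/(1 − f). At 0.2, the assumed 60% and 50% would become 75% and 62.5%, and the difference would grow from 10 to 12.5 points. The document does not show which pattern applies.
- A reader might connect the persistent risk of relapse mentioned in the Background with comorbidities. That sentence concerns obesity itself.
- A reader might take the power column as a refutation of the Discussion's power claim. The rates and the numbers affected are assumed, so it shows only how sensitive such a claim is to the definition.

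**Conclusion.** The point holds in limited form. As written, the general remission rule classes a symptom-free, drug-free patient as remitted whatever the recorded value, for every comorbidity except dyslipidemia and T2DM. Absolute remission rates in both arms can be overstated by (1 − R) f. With f equal across arms, the difference is multiplied by (1 − f).

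The actual size cannot be derived from the document, which gives neither remission rates nor f, nor the number of patients with each comorbidity. The conclusion also assumes that at least one usually silent comorbidity other than these two is among those assessed. Neither primary endpoint nor the 400 per group is affected. This is an inexpensive correction to a secondary endpoint, worth making because remission of comorbidities is part of the stated aim.

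**What to change.** Extend the dyslipidemia logic already in the text. For each comorbidity with an objective measure that the trial already records, count remission only if the patient is off medication and the recorded value lies within a limit fixed in advance. The investigators choose the limit. Replace the slash with an explicit and. Count symptom-free, drug-free patients whose value is outside the limit as not remitted, and state which of the other categories they enter. If the full protocol already contains such criteria, it is enough to state them with the definition.

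This changes endpoint classification only, not patient treatment. It costs a sentence or two and no extra visit, since vital signs and laboratory tests are scheduled at all 11. The downside is that reported remission percentages will be lower.
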